##### Strategy 1: training for therapists

The training for the therapists will consist of three components linked to the determinant analyses in Phase 1: FTE principles and how to provide group training for the elderly, recruitment of elderly, and providing FTE in a financially sustainable way. Each topic is described in more detail below.

a) Training in FTE principles

A critical conclusion of our determinant analysis was that therapists need to learn about the FTE approach. Therapists will therefore be taught the principles underlying FTE. The education module incorporates cooperative learning, and feedback and evaluation. FTE principles will be taught first. This includes the theoretical background, as well as the planning of group progress, documentation of individual progress and the use of clinimetric measures to document changes and plan progress. Secondly, the use of FTE will be demonstrated by teachers with 10 or more years of experienced. Thirdly, the therapists will practise FTE skills and using FTE themselves. The therapists will receive feedback from the teachers about their performance. During the training, the therapists will also be made aware of the importance of giving their participants a range of options to remain active after the FTE programme such as joining social, hobby or activity groups that match the personal needs of the participants and encourage them to stay active.

The determinant analysis showed that it was necessary to train knowledge and skills relating to the target population of elderly people because specific skills are required when addressing the problems faced by older people. The training will therefore focus on social, communicational, motivational and safety issues. Therapists will also learn how to provide group training for the elderly. In line with the determinant analysis, the FTE programme will be adapted to the needs of the participants and the circumstances of the therapists’ local settings. However, key activities and the FTE principles in the programme will not be changed.

b) Recruitment of elderly participants

Therapists will receive training and guidance in building community networks for contacting and recruiting the elderly for FTE. Therapists will be made aware of the different ways of contacting the elderly: through GPs, home care, the community, private care, media and so on. The therapists will learn how to develop a network strategy that is adapted to their local situation. After the training, the network strategy will be immediately applicable and ready to use.

c) Business case

It is important for the FTE programme to be delivered in a way that is financially sustainable for both therapists and the elderly. Financial sustainability was found to be a critical determinant reported by the elderly and the therapists: the programme will not be provided routinely if the costs are too high. The therapists will learn how to draw up a business case (a detailed plan of how to implement FTE, including the expected time, costs, financing, and risks) specifically for their own practice. This means that the business case will be immediately applicable and ready to use during and after the training.

Four teachers will be responsible for the training. Each teacher has his/her own specialty, i.e. FTE principles and application, building community networks, business case development, and group training for elderly. The therapists will receive 20 hours of training over three days. Homework assignments relating to each topic covered by the course will be given and the assignments will be discussed on the next day of training. Therapists will spend an average of 20 hours on homework assignments.

Meetings will be at two-week intervals so that therapists have enough time for the assignments and to familiarise themselves with the FTE principles. At the same time, an online forum will be available for asking questions and sharing information. Therapists will receive support during the implementation process to enhance the likelihood of successful implementation.

##### Strategy 2: adaptation of FTE

The intensity of the programme (number of sessions per week) and the group size will be adapted in the light of the critical remarks that emerged from the determinant analysis. As the determinant analysis showed, the elderly will not automatically see themselves as the target population for FTE. To further acceptance, the FTE programme will be presented to the elderly as an attractive programme.

#### Analyses

To complete the training, each therapist will be given an individual portfolio containing all homework assignments. The training will be evaluated using questionnaires completed immediately after the training and after the therapists have delivered FTE to elderly people for the first time (see Phase 3).

#### Product

The products of this phase are 1) fifteen physiotherapists and remedial therapists trained to implement and execute the FTE programme in their practices, 2) a feasible programme that is adjusted to the needs of therapists and elderly, 3) sound business cases and community network strategies for each local setting.

### Phase 3: study of the effect of FTE (2011–2012)

#### Objective

The aim of the final stage of this study is twofold; 1) to study the process of implementation in terms of reaching the target population of the physiotherapists or remedial therapists as well as the intended proportion of the elderly population, and 2) to study the implementation, and the effect of the implementation, of the FTE programme in daily practice with regard to physical activity and physical functioning of elderly people (as measured with self-report and physical performance measures).

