**Methods/Design:**

Phase 1: The systematic identification of determinants of the implementation of FTE among therapists and the elderly. A questionnaire study was conducted in a random sample of 100 therapists, and interviews took place with 23 therapists and 8 elderly people (aged 66 to 80 years). The determinants were broken down into four categories: the characteristics of the environment, the organisation, the therapists, and the training programme.

Phase 2: Developing and applying strategies adapted to the determinants identified. Fifteen physiotherapists will be trained to provide FTE and to recruit elderly people living at home. The therapists will then deliver the 12-week programme to two groups of elderly, each consisting of six to twelve people aged 70 years or older.

Phase 3: Study of implementation and the impact. To study the actual use of FTE: 1) therapists record information about the selection of participants and how they apply the key features of FTE, 2) the participating elderly will keep an exercise logbook, 3) telephone interviews will take place with the therapists and the elderly and there will be on-site visits. The effects on the elderly people will be studied using: 1) the Patient-Specific Questionnaire, the Timed Up and Go test and a two performance tests. All tests will be performed at the start of the FTE programme, half way through, and at the end of the programme.

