### Objectives

The objective of the study was threefold. Firstly, to develop an implementation strategy for the introduction of FTE based on the outcomes of an analysis of determinants. Secondly, to apply these strategies and to study the process of implementation in terms of reaching the target population of therapists as well as the elderly. Thirdly, to study the effect of the implementation of the FTE programme in daily practice in terms of physical activity and the physical functioning of the elderly population. An innovation framework was used to structure each step and this has been described in the methods section.

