##### Evaluation of the use of FTE

Determinants of use. Before and after the FTE programme, all therapists will receive a questionnaire looking at the determinants of the use of FTE, as well as intentions about the continued use of FTE.

Actual use. The actual use, and the quality of use, of the key activities in the FTE programme will be assessed in three ways: 1) the therapists will complete a record form for each group, detailing the selection of participants, how well they managed to apply the key features of FTE, and what obstacles and facilitating factors were encountered, 2) the participating elderly will keep a logbook of exercises for each training session in which they will note the exercises, the variations that were used, the number of repetitions, the weight used, the perceived intensity of the exercise, and the time needed to perform an exercise, 3) telephone interviews (with therapists and elderly) and site visits will take place in which the researchers will verify the implementation of the FTE, implementation problems and local solutions.

The use of several sources of information will make it possible to study the use of FTE, as well as changes in use resulting from, for example, increased therapist experience with FTE. Furthermore, the completeness of use – the number of activities performed – and the quality of use will be studied.

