##### Effects of the adjusted FTE

Therapists will recruit the elderly and train them using the FTE programme. Before the start of the FTE programme, there will be an intake procedure to check for comorbidities and other limiting factors. During the intake and at the start of the FTE programme, the following questionnaire and tests will be used:

the Patient-Specific Questionnaire (PSQ – in Dutch, the “PatientSpecifiekeKlachtenlijst”) measures the functional status of a patient with respect to the three to five most important physical complaints [26];

the Timed Up and Go test (TUG) measures the basic mobility of older people [27];

the 10 meter walking test measures the walking speed;

a patient-specific performance test (related to the goals of the patient as determined by the PSQ). This test can be different for each participant since it is related to their specific, personal physical problem.

The PSQ questionnaire and the tests will be repeated halfway and at the end of the FTE programme in order to document changes and to provide the therapist with additional information about how to adjust training intensity.

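### Physical activity is named as an effect outcome of Phase 3, but none of the four effect measures records the amount of physical activity

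*Protocol article*

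**What the plan says.** The Objectives section at the end of the Background states the third objective as the effect of implementing FTE in daily practice, "in terms of physical activity and the physical functioning of the elderly population". The Phase 3 Objective repeats the pair and adds the kind of measurement: "with regard to physical activity and physical functioning of elderly people (as measured with self-report and physical performance measures".

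The Phase 3 section on the effects of the adjusted FTE names the instruments. The PSQ "measures the functional status of a patient with respect to the three to five most important physical complaints". For the others it gives "the Timed Up and Go test (TUG) measures the basic mobility of older people", "the 10 meter walking test measures the walking speed", and "a patient-specific performance test (related to the goals of the patient as determined by the PSQ", the last of which may differ between participants. The questionnaire and tests are taken at the start, halfway and at the end. The abstract gives a matching list: "the Patient-Specific Questionnaire, the Timed Up and Go test and a two performance tests".

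Exercise is recorded elsewhere in Phase 3. Under the evaluation of the use of FTE, "the participating elderly will keep a logbook of exercises for each training session", with repetitions, weight, perceived intensity and time. Under the evaluation of the process of implementation, therapists record attendance and reasons for absence. The Phase 3 Analysis section assigns repeated-measures ANOVA to the effect of the programme and names no variable.

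**The concern.** Physical functioning is what a person can do. Physical activity is how much, how often or how intensely the person does it. Either can change without the other, so a faster walk or a better PSQ score does not show that someone has become more active.

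The distinction matters here because activity is a large part of the rationale. The Background cites about 20% of older people in the Netherlands as inactive and presents raising activity as the reason for studying FTE. The study is also meant to inform a national implementation strategy. If the plan is followed as written, the activity part of the third objective goes unanswered, or functional scores or logbook entries are reported as if they answered it.

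**Working it through.** No arithmetic is involved and the plan gives no figure to reproduce. The check sets each Phase 3 data source beside the construct that the article assigns to it, and asks whether the source could yield a change in physical activity.

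| Phase 3 source | What the article says it covers | Role assigned | Measures change in amount of activity? |
|---|---|---|---|
| PSQ | Functional status on three to five complaints | Effect | No |
| Timed Up and Go | Basic mobility | Effect | No |
| 10 m walk | Walking speed | Effect | No |
| Patient-specific performance test | Performance related to personal goals | Effect | No |
| Exercise logbook | Exercises within each training session | Use of FTE | No: sessions only, no value before the programme |
| Attendance records | Presence and reasons for absence | Process | No: sessions only, no value before the programme |
| Telephone interviews and site visits | Verification of implementation, problems and local solutions | Use of FTE | No |

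1. The objective names two effect constructs. The count for functioning is 4 of 4 effect measures and for activity 0 of 4, so 1 of the 2 constructs has no effect measure.
2. The Phase 3 Objective promises self-report as well as performance measures. The only self-report effect measure is the PSQ, which the article defines by functional status, so it does not supply the activity outcome.
3. Repeated-measures ANOVA needs the same quantity on each person at successive occasions, here start, halfway and end. The logbook begins with the first session, so it has no starting value. Its entries describe the exercise that the programme delivered and not a response to it.
4. Daily physical activities are asked about in the article only in the Phase 1 telephone interviews with eight elderly people. Those interviews served the determinant analysis and are not a baseline for the Phase 3 participants.
5. The gap is not explained by an article condensing a longer protocol. The article lists its effect measures in the abstract and again in the methods, the lists agree, and it states the two-part objective twice. The mismatch lies between two things that are both on the page.

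**The case against.** The strongest reply is that physical activity is loosely worded here. The article often speaks of activities in the sense of daily tasks, the stated aim of FTE is functional independence, and one bracket on measurement in the Phase 3 Objective covers both terms and fits the PSQ plus the tests. On that reading the objective contains a redundant term and no outcome is missing. This is arguable, but the Background uses physical activity in its ordinary public-health sense, and both objectives join the two terms as separate items. If loose wording is the cause, the remedy is still to correct the wording.

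A second reply is that taking part in FTE is itself physical activity, and that the objective speaks of daily practice, meaning the care setting, without limiting activity to what happens outside sessions. This stands in part. The logbook and attendance records do document supervised exercise, so a reader who inferred that Phase 3 collects no activity data at all would go too far. What those sources cannot give is a change from before the programme.

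A reader might also infer that time spent in sessions displaces usual activity unseen. Nothing in the article supports that, and the point does not rely on it.

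Finally, the gap biases no measured result. The functional outcomes, the process evaluation and the determinant work are untouched, and activity is one part of the third of three objectives. That limits the weight of the point without removing it.

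**Conclusion.** The mismatch is real and contained. One of the two effect outcomes stated for Phase 3 has no effect measure (0 of 4 instruments), so the study as described cannot estimate a change in physical activity. It can still address physical functioning with the measures listed. The article does not support the stronger reading that the study lacks any record of activity or that its functional findings are compromised.

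The conclusion rests on taking physical activity in its ordinary sense of amount of activity, on the article's own description of what each instrument measures, and on the list of effect measures being complete, as its wording and the matching abstract indicate. It does not depend on sample size, variance or dropout.

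**What to change.** Preferred: restrict the effect objective to physical functioning in both the Objectives section and the Phase 3 Objective, and state that functional scores and logbook data will not be presented as an effect on physical activity. This costs a wording change only.

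Alternative, if activity is truly wanted as an outcome: before the first group starts, add one short validated self-report of physical activity outside the FTE sessions. Give it at the same three occasions as the PSQ and name it in the Analysis section for the same repeated-measures model. A starting value cannot be recovered for a group already under way.

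The alternative costs a few extra minutes per participant per occasion (an assumption; the article gives no figure) and no extra visit. It also needs a check against the Study design section, which justifies the absence of informed consent partly by the use of routinely collected data for estimating effects. A questionnaire added for research may not fit that ground and should be cleared with the ethics committee first.

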#### Participants

Each physiotherapist or remedial therapist who completes the training course will deliver the FTE programme to two groups of elderly people. The second group will start when the first group has finished the 12-week FTE programme. To safeguard against possible therapist drop-out, one extra therapist will be trained. Each group consists of six to twelve elderly people aged 70 years or older who have slight problems with activities of daily living. The targeted elderly people will live independently and be willing to follow FTE to improve their independence and their activities of daily living. They will also have to be able to exercise strenuously without being limited by comorbidities or other disabilities.

#### Method

##### Evaluation of process of implementation

The therapists will keep records about how they recruit elderly people and of the reasons for participation/non-participation of the elderly. Furthermore, during the 12-week FTE programme, the therapists will keep records of the number of participants who are present and the reasons for any absence.

##### Evaluation of the use of FTE

Determinants of use. Before and after the FTE programme, all therapists will receive a questionnaire looking at the determinants of the use of FTE, as well as intentions about the continued use of FTE.

Actual use. The actual use, and the quality of use, of the key activities in the FTE programme will be assessed in three ways: 1) the therapists will complete a record form for each group, detailing the selection of participants, how well they managed to apply the key features of FTE, and what obstacles and facilitating factors were encountered, 2) the participating elderly will keep a logbook of exercises for each training session in which they will note the exercises, the variations that were used, the number of repetitions, the weight used, the perceived intensity of the exercise, and the time needed to perform an exercise, 3) telephone interviews (with therapists and elderly) and site visits will take place in which the researchers will verify the implementation of the FTE, implementation problems and local solutions.

The use of several sources of information will make it possible to study the use of FTE, as well as changes in use resulting from, for example, increased therapist experience with FTE. Furthermore, the completeness of use – the number of activities performed – and the quality of use will be studied.

##### Effects of the adjusted FTE

Therapists will recruit the elderly and train them using the FTE programme. Before the start of the FTE programme, there will be an intake procedure to check for comorbidities and other limiting factors. During the intake and at the start of the FTE programme, the following questionnaire and tests will be used:

the Patient-Specific Questionnaire (PSQ – in Dutch, the “PatientSpecifiekeKlachtenlijst”) measures the functional status of a patient with respect to the three to five most important physical complaints [26];

the Timed Up and Go test (TUG) measures the basic mobility of older people [27];

the 10 meter walking test measures the walking speed;

a patient-specific performance test (related to the goals of the patient as determined by the PSQ). This test can be different for each participant since it is related to their specific, personal physical problem.

The PSQ questionnaire and the tests will be repeated halfway and at the end of the FTE programme in order to document changes and to provide the therapist with additional information about how to adjust training intensity.

#### Analysis

Qualitative analyses will be used to evaluate the implementation strategy. ANOVA for repeated measures will be used to determine the effect of the FTE programme.

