### Intervention: FTE exercise programme

A functional task exercise programme for the elderly (FTE) has been developed and tested [10-12,14]. FTE is a group-based exercise programme to be provided by physiotherapists or remedial therapists (such as Cesar therapists or Mensendieck therapists). It directly targets daily tasks in the domains that are affected early in the aging process. The aim of FTE is to increase the functional independence of older adults in daily life. The programme specifically targets four domains:

1. movements with a vertical component like walking up stairs,

2. movements with a horizontal component like walking around,

3. transporting an object,

4. transfers, for example moving from a lying/sitting/standing position.

During each training session, the participants perform tasks from at least two of the four domains. Each exercise includes three sets of 5–10 repetitions. The 12-week programme is divided into three phases; a practice phase, a variation phase, and a daily tasks phase, therefore increasing the complexity and variability of the exercises step by step. The three phases are described here in brief.

*Practice phase* (2 weeks). The aims of the practice phase are for participants to 1) learn how the exercises are performed, 2) get used to training, and 3) learn how to train at an appropriate intensity. Exercises in this phase consist of short, simple tasks from all four domains: the basic tasks.

*Variation phase* (4 weeks). The aim of the variation phase is to build up the participants’ physical capacities and their ability to use variation and complexity in tasks. In the variation phase, participants apply the basic tasks to various training conditions. Environmental factors are influenced (this involves, for example, distraction using sounds or irregular floors), attributes are used (for example, a shopping bag is used during walking, or something is picked up from the floor), and interaction between participants is encouraged to distract the participants from their tasks.

*Daily tasks phase* (6 weeks). The daily tasks phase consists of a combination of the four domains so that the tasks resemble daily tasks as much as possible. The aim of this phase is to train situations that closely match the participants’ daily activities. Activities are trained beyond the level of variation and complexity that is generally needed for daily activities in order to build up reserve capacity.

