#### Method

##### Recruitment

Specialists in the area of geriatric physiotherapy and remedial therapy will be asked to supply contact information for therapists who might be interested in the study.

The professional organisations of geriatric physiotherapists and remedial therapists will be asked to supply addresses of therapists who might be eligible and interested in the study. Furthermore, addresses of eligible therapists will be obtained from the internet and physiotherapists in the TNO network will be contacted. These will mainly be physiotherapists who have participated in previous studies of training for the elderly.

All therapists will receive an e-mail containing global information about the study. Those therapists who express interest will be contacted by phone and will receive detailed information about the FTE programme, the training and the study protocol. Therapists will be contacted until 15 therapists are found who are eligible to participate in this study. Other interested therapists will be placed on a reserve list.

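### The repeated-measures ANOVA named for the effect of FTE makes no allowance for change being shared among people trained in the same group or by the same therapist

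*Protocol article*

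**What the plan says.** The Analysis section of Phase 3 gives qualitative methods for the implementation strategy and one quantitative method for outcomes: "ANOVA for repeated measures will be used to determine the effect of the FTE programme". It names no term for group or therapist, no multilevel model, no cluster-robust standard error and no ICC.

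Other sections describe a nested design:

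- Intervention section: "FTE is a group-based exercise programme to be provided by physiotherapists or remedial therapists".
- Phase 2, Recruitment: "Therapists will be contacted until 15 therapists are found who are eligible to participate in this study". Phase 3, Participants, adds a reserve: "To safeguard against possible therapist drop-out, one extra therapist will be trained".
- Phase 3, Participants: "Each physiotherapist or remedial therapist who completes the training course will deliver the FTE programme to two groups of elderly people". The second group starts after the first has finished.
- Same section, on size: "Each group consists of six to twelve elderly people aged 70 years or older who have slight problems with activities of daily living".
- Phase 3, Effects of the adjusted FTE: therapists both recruit and train the participants. The questionnaire and tests are taken at the start, halfway and at the end.

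**The concern.** Repeated-measures ANOVA takes out stable differences between persons and judges the time effect against the person-by-time residual. That is valid if one person's change is independent of another's. Participants in the same group share a trainer, sessions and a setting, and those with the same therapist share the trainer and setting across two groups. The protocol lets therapists fit the programme to local circumstances, make tasks harder or easier, and use the test results to adjust training intensity. It also studies how completely and how well FTE is delivered. Some shared variation in change is therefore plausible.

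Only clustering of change matters here. In a one-arm comparison over time, a stable difference in level between groups or therapists cancels.

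If change does cluster, confidence intervals for the mean change are too narrow and p-values too small. This could affect any outcome analysed this way, because no other quantitative effect analysis is named. The results are meant to feed a national implementation strategy, so the precision attached to them matters.

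**Working it through.** The article states no sample size, alpha, standard deviation or ICC for the effect study, so there is no figure to reproduce.

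**Inputs from the article.** 15 therapists, 2 groups each, group size m = 6 to 12, 3 measurement times.

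**Assumptions.** Two-sided alpha of 0.05. ICC of change of 0.02, 0.05 or 0.10, placed wholly at group level or wholly at therapist level.

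**Implied number of participants.** 15 × 2 × 6 = 180 and 15 × 2 × 12 = 360. Using the reserve therapist as well would give 192 to 384. The design effects below do not depend on the number of therapists.

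**Design effect for the mean change.** Let g be the share of change variance at group level and t the share at therapist level:

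DE = 1 + (m − 1)(g + t) + m·t

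The last term is the correlation with the therapist's other group. Examples:

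- Group level, m = 6, g = 0.02: 1 + 5 × 0.02 = 1.10
- Group level, m = 12, g = 0.10: 1 + 11 × 0.10 = 2.10
- Therapist level, m = 6, t = 0.02: 1 + 5 × 0.02 + 6 × 0.02 = 1.22
- Therapist level, m = 12, t = 0.10: 1 + 11 × 0.10 + 12 × 0.10 = 3.30

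**True size of a nominal 5% test.** 2 × [1 − Φ(1.96/√DE)].

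| Clustering at | m | N | ICC 0.02 | ICC 0.05 | ICC 0.10 |
|---|---|---|---|---|---|
| Group | 6 | 180 | DE 1.10, 6.2% | DE 1.25, 8.0% | DE 1.50, 11.0% |
| Group | 12 | 360 | DE 1.22, 7.6% | DE 1.55, 11.5% | DE 2.10, 17.6% |
| Therapist | 6 | 180 | DE 1.22, 7.6% | DE 1.55, 11.5% | DE 2.10, 17.6% |
| Therapist | 12 | 360 | DE 1.46, 10.5% | DE 2.15, 18.1% | DE 3.30, 28.1% |

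The true standard error is √1.10 = 1.05 to √3.30 = 1.82 times the one reported under independence.

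**Check by simulation.** 2000 runs per setting, no true time effect, three times, 15 therapists with two groups each.

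- A t-test on each participant's start-to-end change at m = 12 rejected in 7.6%, 12.7% and 15.7% of runs (group level, ICC 0.02, 0.05, 0.10), and in 10.3%, 18.0% and 27.3% (therapist level). This is close to the formula.
- The three-time repeated-measures ANOVA on participants rejected more often at m = 12: 9.0%, 15.0% and 22.7% (group level), and 13.3%, 25.1% and 41.1% (therapist level). These figures depend on how the shared variation is spread over the three times, so the conclusion rests on the formula.
- With ICC 0, the participant-level ANOVA rejected in 4.9% to 6.2% of runs. Without clustering of change there is no inflation.
- The same ANOVA on the 15 therapist means rejected in 3.6% to 6.0% across all settings.

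**The case against.** The strongest reply is that one sentence in a condensed article is being read for what it omits. It does not say that participants are independent, or that group and therapist are left out. An analysis plan that is not shown could add such terms. This stands as a limit. But the article does choose a method, and in its standard form that method does not handle this nesting.

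The size also rests on assumptions. The ICC is not in the article, and therapist-level clustering is the harsher case. With group-level clustering the low end is only 6.2%. Local adaptation is bounded, since the core activities and principles are to stay fixed. Two of the four measures, the Patient-Specific Questionnaire and the patient-specific performance test, are individualised, so a single ICC range for all outcomes is doubtful. All of this stands, and is why a range is given.

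The practical harm may be modest. At a therapist-level ICC of 0.10, the effective sample size is still 180/2.10 = 86 to 360/3.30 = 109. The 95% half-width is then about 1.96/√86 = 0.21 to 1.96/√109 = 0.19 standard deviations of change. Only a small mean change would lose significance. This also stands, and it lowers the urgency.

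A reader might infer more than the text supports:

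- **That the analysis ignores a question the protocol asks about therapist experience, by pooling first and second groups.** The relevant text speaks of "changes in use resulting from, for example, increased therapist experience with FTE". That concerns use of the programme, which is studied through record forms, logbooks, interviews and site visits, and not participant outcomes. Nor does the article say how the two groups enter the ANOVA.
- **That the overall time test answers the wrong question.** The objectives name no start-to-end contrast, and follow-up contrasts are routine with this method.
- **That there are in effect only 15 observations.** With 9 per group (270 people) and a therapist-level ICC of 0.05, the design effect is 1 + 8 × 0.05 + 9 × 0.05 = 1.85 and the effective sample size is 270/1.85 = 146.

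**Conclusion.** The concern holds in a limited form. The named method, applied in its standard form, does not allow for shared variation in change within groups or therapists, and the design makes such variation plausible. For an assumed ICC of change of 0.02 to 0.10, the true size of a nominal 5% test is about 6% to 18% if clustering is by group and about 8% to 28% if it is by therapist. The direction of the error requires positive clustering of change. The size requires the assumed ICC and alpha.

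This should be fixed, but it is not critical: the study is uncontrolled and states no alpha or power. A reader might also take corrected standard errors as making the change attributable to FTE. They would not, because there is no control group.

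**What to change.** State in the Phase 3 Analysis section that the effect analysis accounts for clustering of change by therapist, and name one of these:

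1. **Therapist means.** Average each outcome over a therapist's participants at each time. Then use either a one-sample t-test on the therapist-mean changes (14 degrees of freedom with 15 therapists) or the planned repeated-measures ANOVA on those means. This is the simpler route and held its size in the simulation.
2. **Linear mixed model.** Time as a fixed effect, a random intercept for participant, and random variation in change at therapist level, plus group level if it can be estimated. Use small-sample degrees of freedom such as Kenward-Roger. A therapist intercept alone is not enough, because it cancels from the change and leaves its standard error uncorrected. Keep the random part sparse: unstructured three-time covariances at both levels would need 6 + 6 = 12 parameters from 15 therapists and 30 groups, with a risk of singular fits.

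The cost is a change of wording and wider intervals. No new data are needed: therapists complete a record form for each group, so membership should already be known.
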